**Fig. 1 Fig1:**
[figure not shown]
Study protocol timeline and flow chart. MS, multiple sclerosis; PROMs, patient reported outcome measures; CSQ; consultant satisfaction questionnaire

Participants are randomly assigned in a 1:1 ratio to one of two groups:*Intervention group*: All participants randomized to the intervention group will be asked to complete the following validated questionnaires at baseline and approximately every 6 months for a total of 12 months:Hospital Anxiety and Depression Scale (HADS) score [24]Quality of life as measured by EuroQol five-dimensional questionnaire (EQ5D) [25]Fatigue as measured by Modified Fatigue Impact Scale (MFIS) [26]The Patient Determined Disease Steps (PDDS) [27]Patient Health Questionnaire-9 (PHQ-9) [28]Open ended text response to (limit 280 characters) “What are the top 3 things you would like your MS healthcare provider to know about you right now?” – to be referred as the 3-item prompt (3IP). Completed questionnaires will be sent to the treating provider via a secured link using encrypted email to review the corresponding scores and the text response to the 3IP.*Conservative group*: All participants randomized to the conservative group will be asked to complete the same questionnaires as above, however only at baseline and at the end of the study at 12 months. Additionally, the treating provider will only be prompted to review the text response to the 3IP and will not be able to access the PROM questionnaire scores.

For both groups, providers will be able to document via REDCap whether they have reviewed the aforementioned items and their response/intervention, if applicable (Supplementary Fig. 3). Examples of provider responses would be phone calls to patients, scheduling earlier appointments, alterations to medication regimens, referral to another health or medical provider, and/or messaging the patient via secure email messaging system; a free text response will also be included to allow documentation of alternative interventions if required. Due to initial lack of provider engagement, providers will be incentivized with token of appreciation ($10 Amazon gift card) for each instance of documenting they have reviewed (and if applicable, enacted healthcare provider intervention in response to) their patients’ PROM scores and/or text responses to 3IP. There will be no difference in incentive if providers offer an intervention (eg. telephone call, referral to another healthcare provider or service, etc.).

Additionally for both groups, critical absolute scores or decrement in subsequent scores as measured by the aforementioned questionnaires will trigger an automated secured email alert to the patient’s treating MS provider. Critical scores and absolute change in scores considered to be meaningful were determined via analysis of normative data associated with individual PROMs (in a validated population of MS patients when available) (see Supplementary Appendix 1).

All groups will also be asked to complete the Consultation Satisfaction Questionnaire (CSQ) [29] as a measure of provider satisfaction, and the CollaboRATE survey [30] as a measure of shared decision-making, at baseline, and at end of the study at 12 months. At the end of the study, providers will be asked to complete a Provider Exit Survey in regards to their own perception on usage of the study measures in PwMS (Supplementary Fig. 4).

### Outcomes

The primary outcome of this study will be:The difference in change in HADS score between the intervention and conservative group at 12 months.

The secondary outcomes of this study will be:The difference in change in the CollaboRATE shared decision-making survey score and CSQ score between the intervention and the conservative groups at 12 months.Provider exit survey responses at 12 months.

### Data collection

The questionnaires will be delivered electronically to the patient at baseline for both conservative and intervention groups. For patients in the intervention group, questionnaires will be delivered electronically again at 6 months and at the end of the study at 12 months; in the conservative group, questionnaires will be delivered electronically again at the end of the study at 12 months. Initial CSQ and CollaboRATE surveys will be sent to both groups at baseline and at the end of the study. Patients will be sent an email to ask them to complete the questionnaires, with 2 follow-up reminders (1 week and 2 weeks) after the initial electronic contact. For provider exit surveys, mean and median values will be calculated from questions assessed on a Likert scale. Proportion of responses on each multiple choice answers will be determined on the one multiple choice question. Open ended responses will be assessed qualitatively.

Study methods, data management, and biostatical support is supplied by EPICORE Centre, Department of Medicine/Pharmacology, Faculty of Medicine and Dentistry (www.epicore.ualberta.ca). Data for the study will be collected and managed using REDCap at the University of Alberta. REDCap is a secure, web-based software platform designed to support data capture for research studies, providing 1) an intuitive interface for validated data capture; 2) audit trails for tracking data manipulation and export procedures; 3) automated export procedures for seamless data downloads to common statistical packages; and 4) procedures for data integration and interoperability with external sources [31, 32]. Data from administered PROMs through REDCap will allow for centralized data collection capable of export for future analysis.

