### Sample size

Using the validation information in our previous study [23] and the following assumptions of 80% power and a two-sided alpha of 0.05, a total sample size of 356 (178 in each group) will be required to detect effect of 0.298 difference between the intervention and the conservative groups. The same size has been calculated for both HADS-Anxiety score (HADS-A) and HADS-Depression score (HADS-D) by the independent T-test. This study will use the sample size calculated for HADS-A, as it required a larger sample size and to ensure there will be sufficient power for both HADS-A and HADS-D. This sample size will be inflated by 10% to 392 (196 in each group) to account for possible dropouts, losses to follow-up, and withdrawals of consent.

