This study has potential limitations. Firstly, both patients and providers are required to participate on a longitudinal basis for a minimum of 12 months. For patients, automatically generated email reminders will prompt them to complete their repeat PROMs, but ultimately they must decide to participate on a continuing basis. On a related note, the decision to set the difference in frequency of PROM collection at 6 months and 12 months for interventional and conservative groups, respectively, was based on pragmatic implementation of the study in a clinical setting. The frequency of PROM administration for the conservative group at 12 months reflects standard annualized clinical follow up for stable PwMS at our centre, in line with international [66] and Canadian guidelines [67]. Setting PROM collection frequency at 6 months for the intensive group was preferable from a practical perspective as frequent enough to capture critical PROM scores and changes between annual visits, but not too frequent as to result in disengagement from PwMS or providers. Additionally, while designed to be accessible to incorporate into workflow, monitoring patient PROMs can only be performed by accessing REDCap, which is separate from EMRs in clinical use at our sites. This will add time and cognitive labour for providers, and an increased frequency of PROM collection may present a practical barrier to clinical use [68]. By setting PROM collection for the interventional group at 6 months, this will ideally allow a more protracted timeframe to integrate a novel clinical tool for providers.

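### The 12-month HADS, the primary outcome, is collected only in the full digital questionnaire round with two email reminders; a HADS-only fallback link in both arms would cheaply reduce missing primary data

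*Protocol article*

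**What the plan says.** **Outcome.** Outcomes defines the primary outcome as "The difference in change in HADS score between the intervention and conservative group at 12 months".

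**Where HADS sits.** Design lists HADS as one of the questionnaires that intervention patients "will be asked to complete the following validated questionnaires at baseline and approximately every 6 months for a total of 12 months". The others are EQ5D, MFIS, PDDS, PHQ-9 and a short free-text prompt. CSQ and CollaboRATE are added at baseline and 12 months. In the intervention arm the completed scores go to the provider. In the conservative arm the provider is prompted to read only the free text. Critical-score alerts apply to both arms.

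**Rounds.** Data collection says that for the intervention arm "questionnaires will be delivered electronically again at 6 months and at the end of the study at 12 months", and that "in the conservative group, questionnaires will be delivered electronically again at the end of the study at 12 months".

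**Follow-up of non-responders.** One scheme is given, without distinction by round or arm: an email "with 2 follow-up reminders (1 week and 2 weeks) after the initial electronic contact".

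**Acknowledged risk.** The limitations in the Discussion say that "automatically generated email reminders will prompt them to complete their repeat PROMs, but ultimately they must decide to participate on a continuing basis". They add that the 6-month interval was chosen partly to avoid disengagement, and that a digital-only format may limit lasting follow-up of some participants.

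**Allowance and missing data.** Sample size adds 10% "to account for possible dropouts, losses to follow-up, and withdrawals of consent". Data analysis says that once cumulative missingness exceeds 10%, the last observation is carried forward.

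**The concern.** The primary endpoint depends on a form that is also part of the intervention, and it has no collection route of its own. Contact described for the 12-month round ends two weeks after the first email, with the same effort as any other round. The patients at risk are those in either arm who have stopped responding, or who would answer a short form but not the whole 12-month set.

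Two things are at stake. The first is precision. The second, which matters more, is comparability of the arms: the intervention arm alone has an extra round and routine sharing of scores, so reasons for not responding may differ, and the stated missing-data rule fills gaps differently in the two arms.

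**Working it through.** **1. The plan's own figure.** Inputs from Sample size: difference 0.298 (no units given; read as standardised, SD = 1), 80% power, two-sided alpha 0.05, independent t-test, 1:1 allocation.

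- Normal approximation: n per arm = 2(1.960 + 0.842)² / 0.298² = 176.8, so 177.
- t-test version: 177.7, so 178 per arm, 356 in total. Power at 178 is 80.1%.
- 178 × 1.10 = 195.8, so 196 per arm, 392 in total.

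Both stated totals reproduce. If exactly 10% are lost, 196 × 0.90 = 176.4 per arm remain and power is 79.7%, an immaterial shortfall.

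**2. Illustrative effect of loss on power.** The document gives no expected 12-month completion rate, so the loss rates below are assumptions. Power is for a complete-case t-test with loss unrelated to outcome and 196 per arm randomised.

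| Loss, conservative / intervention | Observed per arm | Power |
|---|---|---|
| 10% / 10% | 176.4 / 176.4 | 79.7% |
| 20% / 20% | 156.8 / 156.8 | 74.9% |
| 30% / 30% | 137.2 / 137.2 | 69.1% |
| 10% / 30% | 176.4 / 137.2 | 74.2% |

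The second and fourth rows have the same total loss and nearly the same power. Unequal loss matters for bias, not chiefly for power.

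**3. Illustrative bias.** Suppose intervention-arm non-responders do worse than responders by g, with no such gap in the conservative arm. The complete-case estimate shifts by loss × g. With g assumed at 0.25 to 0.5 SD, 20% loss gives 0.20 × 0.25 = 0.05 to 0.20 × 0.5 = 0.10 SD, and 30% loss gives 0.075 to 0.15 SD, against a target of 0.298. The gap and its sign are assumptions.

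**4. What the carry-forward rule does.** Above 10% missing, the rule replaces the complete-case analysis. Set the two schedules beside it:

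| Patient without a 12-month HADS | Last score available | Change entered |
|---|---|---|
| Conservative | Baseline | 0 |
| Intervention, answered month 6 | Month 6 | Baseline-to-month-6 change |
| Intervention, skipped month 6 | Baseline | 0 |

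Let the true mean change be identical in both arms: c at month 12 and c6 at month 6. Let a fraction m be missing at month 12 in each arm, at random, and let a fraction q of the missing intervention patients have a month-6 score.

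- Conservative mean: (1 − m)c + m × 0
- Intervention mean: (1 − m)c + m × q × c6
- Difference: m × q × c6

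So even with no treatment effect and equal, random loss, the rule creates a difference whenever scores have moved by month 6. With q = 1 it is 0.20 × c6 at m = 0.20 and 0.30 × c6 at m = 0.30. The document does not give c6. Each 12-month HADS actually observed removes one such imputed value.

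**The case against.** Much of the case on the other side stands.

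- **Stopping and endpoint loss.** A reader might infer that tiring of the PROM rounds and losing the primary endpoint are one event. The document does not support that. Data collection sends the 12-month questionnaires by arm and time point, and nothing makes month 6 a condition of month 12. A patient who skips month 6 is still sent the 12-month set.
- **All or nothing.** A reader might infer that a patient must finish every questionnaire or be discarded. No passage says that an incomplete set is rejected.
- **The 10% sentence.** It is a sample-size allowance. It does not say that those who stop the rounds are no longer contacted.
- **Asymmetry.** The conservative arm relies on the same 12-month round and reminders, and it too has provider review of free text and critical-score alerts. Its year without a described round could raise its own loss. The direction is open.
- **Power figures.** They are complete-case, whereas the plan would carry values forward at those loss rates.
- **Condensed article.** The full protocol may hold more on retention. The authors also considered disengagement when choosing the interval.

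These points remove any claim of error or contradiction. They do not remove the point itself, because the article states the 12-month contact scheme and admits its weakness ("ultimately they must decide to participate on a continuing basis"). The carry-forward rule does not supply a 12-month value; it treats the arms differently. If the full protocol has a further route to the 12-month HADS, the sponsor can answer by citing it.

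**Conclusion.** This is a worthwhile, inexpensive improvement to Data collection, not an error. As described, the primary outcome has one digital route, two reminders and no fallback, while the plan itself recognises the risk. Those exposed are patients in either arm who stop responding or will not do the full 12-month set.

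No stated figure is wrong. The size of the problem cannot be determined from the document. Power of about 75% at 20% loss and 69% at 30% is illustrative: it assumes the loss rates, equal random loss, complete-case analysis and a standardised 0.298. The structural part needs no assumed loss rate, only that the carry-forward sentence applies to HADS: the conservative arm can carry only baseline, while the intervention arm can carry month 6.

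A reader might go further and conclude that the trial will suffer differential attrition against the intervention arm. The document has no attrition data, and that conclusion is not supported.

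**What to change.** In Data collection, for the 12-month round and identically in both arms:

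- let the last reminder carry a link to the HADS alone for anyone who has not completed HADS;
- accept it within a fixed window set in advance;
- send it also to patients who stopped the PROM rounds but did not withdraw consent for their data, and state that distinction in the text;
- record the route and date of each 12-month HADS, so that results by route can be examined.

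The cost is one short REDCap instrument and one automated email on the platform already in use. There are two downsides. Some patients will have HADS without the secondary questionnaires, and the 12-month window becomes slightly wider, with some scores given later and in a shorter questionnaire setting by a self-selected group. Applying it equally to both arms and recording the route keeps this visible.

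Trial status reports 191 enrolled at submission of a planned 392, so 392 − 191 = 201 planned participants were still to be enrolled and had their 12-month round ahead.

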### Sample size

Using the validation information in our previous study [23] and the following assumptions of 80% power and a two-sided alpha of 0.05, a total sample size of 356 (178 in each group) will be required to detect effect of 0.298 difference between the intervention and the conservative groups. The same size has been calculated for both HADS-Anxiety score (HADS-A) and HADS-Depression score (HADS-D) by the independent T-test. This study will use the sample size calculated for HADS-A, as it required a larger sample size and to ensure there will be sufficient power for both HADS-A and HADS-D. This sample size will be inflated by 10% to 392 (196 in each group) to account for possible dropouts, losses to follow-up, and withdrawals of consent.

### Data analysis

Prior to conducting statistical analysis, preliminary screening will be conducted using Statistical Analysis System (SAS) 9.4 software (SAS Institute Inc, Cary, NC, USA) to ensure that all the enrolled patients meet the eligibility inclusion and exclusion criteria and confirm the participants provide informed consent. Data assessors will be blinded to participant intervention versus conservative grouping status via de-identified data.

Data analysis will be performed using the computer R 3.4.0 software (Vienna, Austria; https://www.R-project.org/) and SAS 9.4 software. Patient demographic and clinical characteristics will be analysed using descriptive statistics. Categorical variables will be reported using frequency, and percentage and continuous variables will be reported using mean (standard deviation [SD]) or median (interquartile range [IQR]) as appropriate. Univariate level analysis will be conducted to determine if there is a statistical significance between the outcomes (e.g., baseline to six months and 12 months, respectively). Chi-square and Independent T-tests will be used for the univariate analysis, or where appropriate, non-parametric tests (Fishers test and Wilcoxon rank test) will be utilized. Multivariate analysis of variance (MANOVA) will be used to test for overall differences between the intervention and conservative groups at the different time points and variances amongst the variables by groups and time points. All test assumptions will be checked during the data analysis process. Statistical significance will be set at *p* values less than 0.05.

The primary outcome of difference in change of HADS-D and HADS-A, from baseline to 12 months between the intervention and conservative groups, will be tested using an independent T-test. The change of HADS score will be tested by MANOVA for two-way design setting to check if a statistically significant mean of change exists through time points between the groups. The MANOVA helps control for inflation of Type I error (rejection of a true null hypothesis as the result of a test procedure) and count the correlation between sections. Post-hoc Tukey Honestly Significant Difference (HSD) Test will be performed afterwards with adjustment by Bonferroni method, which allows many comparison statements to be made while still assuring an overall confidence coefficient is maintained. Paired T-test will also be considered for use. Regression analysis will be performed to quantify the change of CSQ through time points and between the groups considering patients’ individual effect as random effect. With more than 10% cumulative missing rate, the last observation will be carried forward in the case of missing data. The difference in change in both CSQ score and CollaboRATE shared decision-making survey score, will be analysed using the same methods as described above. The CSQ will be treated as continuous variables with an overall satisfaction score as a sum of the sub-scales for each question in the CSQ.

Linear mixed effect model will be used in multivariable analysis level in order to adjust patients’ individual effect and to quantify the change of outcome measure through time points and between the groups considering the impact of selected variables when they cooperate by presenting the coefficient (standard error), 95% confidence interval, and *P*-values. The variables included in the multivariable analysis will be selected if they were statistically significant on the univariate level analysis and considered clinically significant by the research team.

For provider exit surveys, mean and median values will be calculated from questions assessed on a Likert scale. Proportion of responses on each multiple choice answers will be determined on the one multiple choice question. Open ended responses will be assessed qualitatively.

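### HADS-A and HADS-D are two primary t-tests at an unsplit 0.05 with no either/both rule, and the MANOVA as written does not protect them

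*Protocol article*

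**What the plan says.** - **Outcomes** lists one primary outcome, without naming a subscale: "The difference in change in HADS score between the intervention and conservative group at 12 months".
- **Data analysis** specifies two scales: "The primary outcome of difference in change of HADS-D and HADS-A, from baseline to 12 months between the intervention and conservative groups", which "will be tested using an independent T-test".
- **Data analysis** also sets one threshold for everything: "Statistical significance will be set at *p* values less than 0.05". **Sample size** uses "80% power and a two-sided alpha of 0.05". Neither divides the 0.05 between the scales.
- **Sample size** calculates a size for each scale separately and adopts the larger, for HADS-A, "to ensure there will be sufficient power for both HADS-A and HADS-D".
- **Data analysis** offers one safeguard: "The MANOVA helps control for inflation of Type I error". The MANOVA is described as a test of HADS change over time points between groups. A Tukey test with a Bonferroni adjustment follows it.
- On what counts as success, the wording is mixed. The first hypothesis under Objectives joins depression and anxiety with 'and'; the closing paragraph of the Discussion joins them with 'or'.

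**The concern.** The article fixes the primary test, the significance level and a claim of error control, and these three do not fit together. Two tests at 0.05 hold the overall error at 5% only if both must be significant, or if some procedure links them. No such rule or link is written.

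At stake is how a split result would be read. If one scale reaches p < 0.05 and the other does not, nothing in the article says whether the trial succeeded, so the rule could be chosen after the data are seen. A reader would also take the MANOVA sentence as assurance that multiplicity had been dealt with for the primary tests.

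**Working it through.** **Inputs.** Effect 0.298, 178 per arm, two-sided 0.05 and 80% power come from Sample size. The article gives no SD; the stated size reproduces if 0.298 is a standardized difference, so I take it as one. The correlation between the two change scores and the HADS-D effect are not given. I assume correlations from 0 to 0.9 and, where an effect on HADS-D is needed, the HADS-A value of 0.298.

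**1. The plan's own figure.** n per arm = 2(z₀.₉₇₅ + z₀.₈₀)²/d² = 2(1.960 + 0.842)²/0.298² ≈ 177. With the t distribution it is 177.7, so 178 per arm, as stated. The expected test statistic is 0.298 × √(178/2) = 2.811, and power is Φ(2.811 − 1.960) = 80.3%, or 80.1% with the t distribution. HADS-D needed fewer patients, so its power for its own planned effect is at least that. The 80% is correct for each scale taken singly at 0.05.

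**2. Either scale suffices.** Family-wise error = 1 − P(|Z₁| < 1.96 and |Z₂| < 1.96), with (Z₁, Z₂) bivariate normal. At correlation 0 this is 1 − 0.95² = 9.75%.

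| Correlation (assumed) | Error, either scale at 0.05 | Power for both at 0.05, both effects 0.298 |
|---|---|---|
| 0 | 9.75% | 64% |
| 0.5 | 9.1% | 69% |
| 0.7 | 8.35% | 72% |
| 0.9 | 7.0% | 75% |

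**3. Both scales required.** Error is not inflated. Joint power is in the last column; at correlation 0 it is 0.803² = 64%. Equal effects are the worst case, because HADS-D needed the smaller sample. Joint power rises if the HADS-D effect is larger, but it cannot exceed the 80.1% for HADS-A alone.

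**4. Does the MANOVA protect the t-tests?** Only if they are conditional on it. With two hypotheses, a two-scale MANOVA at 0.05 that must be significant before either t-test is read at 0.05 is a closed test. Simulation with 500,000 draws, at correlations 0, 0.5 and 0.7 and with neither or one scale truly affected, gives a family-wise error of 3.8% to 5.0%. The article does not write this gate.

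**5. Power once the error is controlled, 178 per arm.** At 0.025 for one scale, power is Φ(2.811 − 2.241) = 71.6%, or 71.2% with the t distribution. Under Holm, by simulation on the normal scale, HADS-A power is about 72% if only HADS-A responds. It is about 75–78% if both effects are 0.298 (78% at correlation 0, 75% at 0.9).

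**The case against.** Four points can be made for the plan.

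- **Either-scale success is not documented.** A reader might infer that the trial's false-positive risk is simply above 5%. The article does not support that without a condition: the hypothesis under Objectives can be read as requiring both scales, and then 0.05 for each is sound. This stands, so the inflation is stated only for the either-scale rule, which the Discussion's wording leaves open.
- **The power statement is not false.** A reader might infer that 80% power for the two scales is not delivered. Sample size makes a calculation per scale and never claims joint power, and step 1 confirms it. This stands in full.
- **Inflated error and low joint power cannot both be charged.** They belong to different success rules. This stands; they are put here as alternatives.
- **Multiplicity is addressed, and testing order is often left to the analysis plan.** The article does mention MANOVA, correlation between sections and Bonferroni, and a two-scale MANOVA could work as a gate. It would therefore be wrong to say that MANOVA cannot control the error. But the Bonferroni step is tied to the post-hoc Tukey test, and the primary t-tests are stated on their own terms. An unseen plan might supply the link, but the article itself makes the claim of control, and what it describes does not deliver it for the primary tests.

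**Conclusion.** The point holds in this form: one primary outcome is named, two are tested at an unsplit 0.05, the success rule is missing, and the stated safeguard does not reach the primary t-tests as written.

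The size depends on the rule the sponsor intends. If either scale suffices, family-wise error is about 7.0% to 9.75% for correlations from 0.9 down to 0. If both are required, error stays within 5%, and joint power is about 64–75% with both effects at 0.298 and at most about 80% otherwise. Both ranges rest on assumed correlations, and the joint-power range also rests on the equal-effect worst case. That some rule and link are needed rests on neither assumption.

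**What to change.** 1. **Outcomes:** name change in HADS-A and change in HADS-D at 12 months as the two primary outcomes, and state that either can support a claim.
2. **Data analysis:** test the two by Holm at an overall two-sided 0.05. Alternatively, state that a two-scale MANOVA of the 12-month changes at 0.05 must be significant before either t-test is read at 0.05.
3. **MANOVA sentence:** let it claim error control for the primary tests only if it is that gate.
4. **Sample size:** keep the 80% as power per scale at an unadjusted 0.05, and add the power under the chosen rule. Under Holm at 178 per arm this is about 72% for HADS-A if only HADS-A responds and about 75–78% if both effects are 0.298. Under the gate, power depends on the correlation and should be calculated over a stated range.

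If the sponsor means that both scales must succeed, the article should say so, keep 0.05 for each and report joint power instead.

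**Cost:** wording, and a stated power below 80%. No extra patients are needed if that is accepted. To restore 80% for HADS-A at 0.025 would take 216 per arm (432 in total, or 432 × 1.10 ≈ 476 with the article's own inflation) against the planned 392.

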### Design

This study is a randomized controlled trial with the patient as the unit of randomization. Patients will be randomized electronically in a 1:1 ratio to the intervention or conservative groups at study enrolment using a native REDCap randomization module to ensure allocation concealment. The timeline of the study protocol is depicted in Fig. 1.

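### The primary HADS comparison is an unadjusted t-test on change; adjusting for baseline HADS, already collected in both arms, would be more precise at the same sample size

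*Protocol article*

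**What the plan says.** The Outcomes section defines the primary outcome as "The difference in change in HADS score between the intervention and conservative group at 12 months". The Data analysis section applies this to HADS-D and HADS-A separately and states that the change from baseline to 12 months "between the intervention and conservative groups, will be tested using an independent T-test". No covariate is named.

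The Sample size section uses the same test. It assumes "80% power and a two-sided alpha of 0.05", aims to "detect effect of 0.298 difference between the intervention and the conservative groups", and concludes that "a total sample size of 356 (178 in each group) will be required". The calculation was done for "HADS-Anxiety score (HADS-A) and HADS-Depression score (HADS-D) by the independent T-test".

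The Design and Data collection sections schedule HADS at baseline in both arms, so the adjusting variable is already in the dataset.

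The Data analysis section also lists a MANOVA of change in HADS and a linear mixed model. Neither is named as the test of the primary outcome, and neither names baseline HADS as a covariate. Covariates for the multivariable model are to be chosen by univariate significance together with the research team's clinical judgement.

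**The concern.** A change score uses baseline with a fixed coefficient of 1. When the 12-month score regresses toward the mean, the best linear coefficient is below 1, and subtracting the whole baseline over-corrects. This has two consequences. The change score carries more residual variance than a baseline-adjusted comparison, so the trial has less power than its data allow. If the arms also differ by chance in baseline HADS, the change-score estimate moves in the opposite direction by part of that difference.

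What is at stake is precision on the primary outcome. Under randomisation both analyses estimate the same arm difference, so the adjusted one needs no change to the trial's question.

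**Working it through.** **Inputs.** From the Sample size section: effect 0.298, two-sided alpha 0.05, power 80%, 178 per arm, independent t-test. From the Design section: 1:1 allocation. Not given, and therefore assumed: the baseline to 12-month correlation r (range shown), equal variances s² at both visits, and the unit of 0.298.

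**Step 1: reproduce the plan's figure.** Take 0.298 as a standardised difference. Normal approximation: 0.298 × √(178/2) = 2.811; 2.811 − 1.960 = 0.851; power = Φ(0.851) = 80.3%. With the noncentral t distribution, power at 178 per arm is 80.1%, and 178 is the smallest n per arm that reaches 80%. The stated 356 in total is reproduced.

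**Step 2: variance under each analysis.**
- Change score: 2(1 − r)s².
- 12-month score adjusted for baseline: (1 − r²)s².
- Ratio, adjusted to change: (1 − r²)/[2(1 − r)] = (1 + r)/2, which is below 1 for every r < 1.

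Without equal variances (SDs s₀ and s₁), change-score variance minus adjusted variance is s₀² + s₁² − 2r·s₀·s₁ − s₁²(1 − r²) = (s₀ − r·s₁)². This is never negative. It is zero only when the regression slope r·s₁/s₀ equals 1. The direction therefore does not rest on the equal-variance assumption, but the size does.

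**Step 3: power at 178 per arm, with 0.298 in SDs of change.** The standardised effect becomes 0.298/√((1 + r)/2). Noncentral t:

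| r | Variance ratio | Power, t-test on change | Power, baseline-adjusted | n per arm for 80%, adjusted |
|---|---|---|---|---|
| 0.5 | 0.75 | 80.1% | 89.9% | 134 |
| 0.6 | 0.80 | 80.1% | 88.0% | 143 |
| 0.7 | 0.85 | 80.1% | 86.0% | 152 |
| 0.8 | 0.90 | 80.1% | 84.0% | 161 |
| 0.9 | 0.95 | 80.1% | 82.0% | 169 |

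A simulation of 4,000 trials per setting agrees: 79.5% against 90.0% at r = 0.5, and 80.2% against 86.0% at r = 0.7.

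**Step 4: the other reading of 0.298.** If it is in SDs of the raw score, power for the change-score t-test against the adjusted analysis (normal approximation) is 66.1% v 83.8% at r = 0.3, 80.3% v 90.1% at 0.5, 88.2% v 94.0% at 0.6, and 95.3% v 97.6% at 0.7. The adjusted analysis is ahead at each of these values.

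**Step 5: chance imbalance in baseline HADS.** The standard error of the baseline difference is √(2/178) = 0.106 SD, so the 1.96-SE limit is 0.208 SD. Given an imbalance of that size, the change-score estimate shifts by (1 − r) × 0.208:
- r = 0.5: 0.104 SD. The SD of change is √(2 × 0.5) = 1.000 SD, so the planned effect is 0.298 SD and the shift is 0.104/0.298 = 35% of it.
- r = 0.7: 0.062 SD. The SD of change is √(2 × 0.3) = 0.775 SD, so the planned effect is 0.298 × 0.775 = 0.231 SD and the shift is 0.062/0.231 = 27% of it.

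At an imbalance of one SE the shifts are about half as large: 0.053 SD and 0.032 SD.

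**The case against.** The strongest reply is that nothing here is wrong. Outcome, sample size and primary test all rest on change and an independent t-test, and the stated n reproduces. That stands, and the point is one of efficiency only.

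A reader might infer that the t-test is biased or invalid because of baseline imbalance. The article does not support that. It states that "Patients will be randomized electronically in a 1:1 ratio", and under that allocation the estimator is unbiased. The shift in step 5 is conditional on the imbalance that happens to occur, and the t-test's standard error already allows for it. Nor does adjustment remove every chance imbalance: it removes the linear effect of imbalance in baseline HADS, not that of other variables.

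A reader might also infer that the precision is needed because alpha is divided between the two subscales. The article divides no alpha in the primary t-tests. It sets significance at 0.05, and its Bonferroni adjustment belongs to the post-hoc comparisons after the MANOVA.

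The size of the gain is open to fair challenge. The correlation, the equal variances and the unit of 0.298 are all assumptions. If 0.298 is in raw-score SDs and r is 0.6 or 0.7, the t-test already exceeds 80% power. If 12-month scores are more variable than baseline, the gain can nearly vanish. The rule to carry the last observation forward once missingness passes 10% would also reduce it. A conservative-arm patient has only a baseline value before month 12, and carrying it forward raises the analysed correlation. These points limit the size and not the direction.

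Finally, an unseen analysis plan might be expected to settle this. But the article does not leave the primary test open; it names one.

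**Conclusion.** The point holds as an improvement that needs no new data. The named primary analysis is valid and correctly sized if 0.298 is in SDs of change, but it is less precise than a baseline-adjusted analysis of the same data. With equal variances and r between 0.5 and 0.8, adjustment cuts the variance by 25% to 10% and lifts power at 178 per arm from about 80% to between 90% and 84%. At r = 0.9 it reaches about 82%, a small gain. Confidence is high in the direction and moderate at best in the size, because the article gives neither r nor the unit of the effect. The mixed model does not meet the point: it is not the primary test, and data-driven selection does not guarantee that baseline HADS enters.

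**What to change.** Name as the primary analysis a linear model of the 12-month score on arm plus the baseline score of the same scale, fitted for HADS-A and for HADS-D. Report the adjusted arm difference with its 95% confidence interval. Treat CSQ and CollaboRATE in the same way, since both are collected at baseline and 12 months and the article gives them the same methods. Keep the independent t-test on change as a supportive analysis.

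The sample size can stay at 356 evaluable, with the gain taken as extra power. No additional data are required. The cost is procedural: the trial is registered and had 191 participants enrolled when the article was submitted, so the change should be recorded as a dated amendment before unblinding.
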